### Secondary outcomes

The secondary outcomes assess the longer term (up to 12 months) effects of the intervention on the following:Acceptable hearing at 6 and 12 months (defined as above).Tympanometry (using calibrated standardised tympanometers and modified Jerger classification Types A, B and C).Otoscopic findings.Healthcare consultations related to OME and other resource use.Grommet surgery at 6 and 12 months.Adverse effects.Symptoms (reported by parent and child if appropriate).Functional health status.Health-related quality of life. Short and longer term cost effectiveness.

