### Analysis

#### Sample size

The sample size calculation is based on demonstrating a change in the rate of resolution of hearing loss at 5 weeks post randomisation (4 weeks post completion of treatment) from 20 % in the control group to 35 % in the intervention group. OME resolves spontaneously in a high proportion of children, and some studies have found a significantly higher rate of spontaneous resolution. For example, Williamson et al. found a resolution rate in their control group of 47 % [16]. However, we anticipate a lower spontaneous rate of resolution because we will only include children who have been symptomatic for at least 3 months and are recruiting children in a secondary care setting, where a more severe spectrum of illness can be anticipated. The Cochrane review of steroids for OME reported a ratio of proportions for resolution of OME at 2 weeks of 3.80 (95 % CI = 0.93 to 15.52). In the five studies in the Cochrane review of oral steroids versus placebo, overall there was a 23 % recovery rate in the placebo plus antibiotic group and a 47 % recovery rate in the oral steroid plus antibiotic group, which represents a 24 % difference (antibiotics on their own are ineffective) [12]. We have selected a conservative estimate of 1.75 for our effect size (ratio of proportions) because we believe that a 15 % absolute increase in the rate of resolution at 5 weeks would represent a clinically meaningful benefit that could result in a meaningful reduction in unnecessary operations and a related saving in cost for the NHS. In order to demonstrate a difference between 20 % and 35 % with an alpha of 0.05 and 80 % power, we will need 302 participants (nQuery software version 4.0). We will recruit 380 to allow for a 20 % loss to follow-up at 1 year. Although our primary outcome data will be gathered at 5 weeks, we believe that it is important to be able to assess long-term outcomes and, therefore, want to ensure that we will have sufficient power for longer term follow-up assessments.

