#### Statistical analysis

The primary analyses will be intention to treat and will employ a logistic regression model to investigate differences in the proportion of children with acceptable hearing at the 5 weeks post randomisation follow-up appointment between the two treatment arms, adjusting for site. Comparisons will be presented as the absolute difference in proportions and the adjusted odds ratio, with 95 % confidence interval and *P* value.

Secondary outcomes with a binary outcome (present/absent), such as satisfactory hearing and presence of effusion, will employ repeated measures logistic regression to investigate differences between the trial arms and over time (5 weeks and 6-month and 12-month follow-ups). Changes in hearing over time will also be analysed to identify children who show early resolution but then relapse. For continuous secondary outcomes, such as PedsQL, and OM8-30 scores, repeated measures linear regression models (using transformations as necessary) will be used to investigate differences between the trial arms and over time (5 weeks, 6 months and 12 months) adjusting for baseline. The duration between the start and the resolution of the symptoms will be calculated and the median (interquartile range) for each randomised group will be presented. A Cox regression model will be used to test whether time to resolution differs between the randomised groups.

A number of outcomes will be calculated from the parents’ diary for the first 5 weeks, such as total time off school/nursery and work (days) and the number of healthcare consultations. These will be analysed using Poisson regression to investigate differences between the two trial arms.

Previous researchers have mapped OM8-30 scores to utility values on the HUI-3 scale. As this trial measures both OM8-30 and HUI-3, it provides the opportunity to evaluate the generalisability of the existing mapping. This will be done by correlating the mapped utility values on the HUI-3 scale (obtained via the mapping formula from the OM8-30 facet scores) with the newly acquired HUI-3 scores.

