Possible confounders such as the child’s age and history of atopy and relevant interaction terms will be entered into the primary regression analyses for each of the outcomes in order to conduct pre-specified subgroup analyses. These subgroups will be defined in advance of any analysis based on the best available evidence. Since the trial is powered to detect overall differences between the groups rather than interactions of this kind, the results of these exploratory analyses will be presented using confidence intervals as well as *P* values. No interim analyses are planned.

Full description of the methods to be used will be stated in a trial statistical analysis plan.

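### Poisson regression is named for the diary counts with no provision for variance above the mean, which is likely for days off and for consultations

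*Protocol article*

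**What the plan says.** The Statistical analysis section of the protocol article introduces a group of count outcomes: "A number of outcomes will be calculated from the parents’ diary for the first 5 weeks". The examples it gives are "such as total time off school/nursery and work (days) and the number of healthcare consultations". One sentence then fixes the method: "These will be analysed using Poisson regression to investigate differences between the two trial arms". It names no variance estimator, dispersion parameter or alternative model.

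The preceding paragraph, on continuous secondary outcomes, does allow for data that fit the model poorly: "repeated measures linear regression models (using transformations as necessary) will be used". The counts get no comparable clause.

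Two further statements bear on the point. The Secondary outcomes section lists "Healthcare consultations related to OME and other resource use", so consultations are a declared secondary outcome. Days off are not listed by name and could fall only under the resource-use part of that item. At its end, the analysis text defers detail: "Full description of the methods to be used will be stated in a trial statistical analysis plan". That plan is not available here.

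**The concern.** A Poisson model sets the variance of a count equal to its mean. The outcomes named are unlikely to behave that way, for three reasons.

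- **Days off come in spells.** One illness typically removes several consecutive days, so the total is a sum of spell lengths and not a count of separate events.
- **Some zeros may be structural.** The children are aged 2 to 8. Some may not yet attend school or nursery, and some parents may not be in paid work, so they can only score zero.
- **Children differ in how often they consult.** Any such variation between children adds to the Poisson variance.

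Each of these pushes the variance above the mean. The estimated rate ratio is not biased by overdispersion alone, but its model-based standard error is too small. What is at stake is a chance difference between arms in time off or consultations being reported as a treatment effect with a misleadingly narrow interval.

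**Working it through.** **1. The plan's own figure.** The article gives no mean, variance, dispersion or power for any count outcome. The only figure to reproduce is the primary sample size: "difference between 20 % and 35 % with an alpha of 0.05 and 80 % power, we will need 302 participants". It is used here only to set the group size in step 5.

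- Without continuity correction, two-sided: n = [1.96 × √(2 × 0.275 × 0.725) + 0.8416 × √(0.20 × 0.80 + 0.35 × 0.65)]² / 0.15² = (1.2377 + 0.5239)² / 0.0225 = 137.9, so 138 per arm, 276 in total.
- With continuity correction: (137.9 / 4) × [1 + √(1 + 4 / (137.9 × 0.15))]² = 150.9, so 151 per arm, 302 in total. This matches the stated figure.
- Allowing 20 % loss: 302 / 0.80 = 377.5, so 378. The article rounds to 380.

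**2. Why phi exceeds 1 for these outcomes.** Let phi = variance / mean.

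- *Spells.* If the number of spells is Poisson and each lasts X days, phi = E[X²] / E[X]. This equals 1 only if every spell lasts exactly one day. Illustration (assumed): 0.5 spells per child on average, each lasting 1 + Poisson(1.5) days. Then E[X] = 2.5, E[X²] = 1.5 + 2.5² = 7.75, and phi = 7.75 / 2.5 = 3.1.
- *Structural zeros.* If a fraction p can only score zero and the rest are Poisson with mean λ, phi = 1 + pλ.

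**3. Effect on the test.** The Poisson model gives the log rate ratio a standard error of √(1/A + 1/B), where A and B are the total counts in the two arms. If the variance is phi times the mean, the true standard error is √phi times that. With no treatment effect, the true two-sided error of a nominal 5 % test is therefore 2 × [1 − Φ(1.96 / √phi)], and the coverage of a nominal 95 % interval is one minus this.

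**4. Results by assumed phi.**

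| phi (assumed) | true SE / model SE | true error of 5 % test | coverage of 95 % interval |
|---|---|---|---|
| 0.8 | 0.89 | 2.8 % | 97.2 % |
| 1.0 | 1.00 | 5.0 % | 95.0 % |
| 1.2 | 1.10 | 7.4 % | 92.6 % |
| 1.5 | 1.22 | 11.0 % | 89.0 % |
| 2 | 1.41 | 16.6 % | 83.4 % |
| 3 | 1.73 | 25.8 % | 74.2 % |
| 5 | 2.24 | 38.1 % | 61.9 % |

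**5. Check by simulation.** This used 151 children per arm, no treatment effect and 4,000 data sets per setting.

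- Model-based Poisson standard errors: 4.9 % error with truly Poisson counts. With negative binomial counts, 10.7 % at phi 1.5, 17.0 % at phi 2, about 25 % at phi 3 and 38.5 % at phi 5. The spell illustration (phi about 3.1) gave 25.8 %.
- Robust or Pearson-scaled standard errors: between 4.7 % and 5.7 % in every setting.

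**The case against.** The strongest reply is that this is a condensed article that defers full methods to a statistical analysis plan not shown here. Dispersion checks, variance estimators and fallback models are commonly settled in such a plan, so their absence from the article is not in itself an error. Nor does naming Poisson regression rule out robust or scaled standard errors; a Poisson model with robust errors is one of the remedies proposed. And no dispersion figure is given, so nobody can say from the documents that the intervals will be wrong.

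Much of this stands. It limits the point to a conditional one: the error arises if the counts are overdispersed and model-based errors are used. It does not remove the point, because the article commits to a named model for named outcomes. Unqualified, that name ordinarily means model-based errors, and a later plan would normally carry it forward.

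A reader might infer three stronger things that the documents do not support.

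- *That partly completed diaries are counted as low use, because no exposure term is mentioned.* The article lists no terms for this model and does not say how incomplete diaries are handled. This is silence that an analysis plan would fill.
- *That spurious differences would feed the cost-effectiveness result.* The Economic analysis section costs resource use from questionnaires with published unit costs and examines uncertainty by sensitivity analysis. It does not describe any Poisson interval or P value as an input.
- *That the model lacks covariates it needs.* Nothing in the overdispersion argument bears on covariate choice.

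**Conclusion.** The point holds in conditional form. The named method is poorly matched to the named outcomes, and the article attaches no safeguard to it. Variance above the mean is the expected case for days off and likely for consultations.

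If it occurs and is not corrected, the effect is material even when mild: the false-positive rate about doubles at phi = 1.5 (11 %) and reaches 17 % to 38 % for phi from 2 to 5. These phi values are assumptions. At phi = 1 the test is correct, and below 1 it is conservative, so it would go too far to say that the intervals will certainly be too narrow.

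Only secondary diary outcomes are affected. The logistic analysis of acceptable hearing at 5 weeks and the sample size of 302 evaluable (380 recruited) children do not depend on it. This is a modest point, worth correcting because the correction is cheap.

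**What to change.** Replace the sentence on Poisson regression with one stating that the diary counts will be analysed by negative binomial regression, or by Poisson regression with robust or scaled standard errors, and reported as rate ratios with 95 % confidence intervals. If the analysis plan already says this, confirm it there and align the two texts.

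The cost is one sentence, with no change to data collection, sample size or primary analysis. Intervals widen by about √phi: hardly at all if the counts are close to Poisson, about 22 % at phi = 1.5 and 41 % at phi = 2. That extra width is uncertainty which the model-based interval would have left out.

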#### Economic analysis/cost effectiveness analysis

The cost-effectiveness analysis will be conducted from the perspective of the UK NHS and Personal Social Services and also will consider a broader partial societal perspective, encompassing impacts on patients and their families. The cost-effectiveness component will have two time durations: a within-trial assessment and a longer term time horizon based on decision-analytic modelling and populated from parameter estimates derived from the trial and from information from literature sources relating to long-term effects of hearing difficulties in children. These time periods offer a longer duration than previous studies and will be used, alongside other sources, to arrive at more meaningful estimates of cost-effectiveness.

The costs of the course of oral steroids will be calculated and combined with differences in costs between intervention and control groups to determine overall costs associated with the intervention. The resource utilisation of both groups (consultations, medications, operations, equipment, etcetera) and treatments associated with adverse events, will be assessed through the completion of self-completed questionnaires at baseline, at 5 weeks, 6 months and 12 months and translated into costs using appropriate published unit costs [29].

The difference in overall costs between groups will be compared with differences in outcomes, as specified above, and including quality-adjusted life years (QALYs). QALYs will be computed from PedsQL and HUI 3 and from utilities derived from mapping responses to the OM8-30 questionnaire [30].

A series of one-way sensitivity analyses will be conducted to assess the impact of parameter variation on baseline estimates of the cost-effectiveness ratios and a probabilistic sensitivity analysis undertaken to determine the extent to which the intervention can be regarded as representing value for money.

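### Correlation cannot show whether the existing OM8-30 to HUI-3 mapping generalises, because it measures association and not agreement

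*Protocol article*

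**What the plan says.** In the protocol article, under Statistical analysis, the trial's collection of both OM8-30 and HUI-3 is given a methodological use: "it provides the opportunity to evaluate the generalisability of the existing mapping". The method follows at once: "This will be done by correlating the mapped utility values on the HUI-3 scale". The mapped values are "obtained via the mapping formula from the OM8-30 facet scores", and they are to be correlated "with the newly acquired HUI-3 scores". No measure of error, bias or calibration is named.

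Under Economic analysis/cost effectiveness analysis, the mapped values have a second role: "QALYs will be computed from PedsQL and HUI 3 and from utilities derived from mapping responses to the OM8-30 questionnaire". HUI-3 is thus both the yardstick for the mapping and a direct source of QALYs.

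The same analysis section ends with a deferral: "Full description of the methods to be used will be stated in a trial statistical analysis plan". That plan was not available here.

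**The concern.** A mapping onto a utility scale generalises if, in new children, the utilities it predicts are close to the utilities observed. That is a question of agreement on an absolute scale. Correlation answers a different one: whether children with higher mapped values also tend to have higher observed values. A low correlation would count against the mapping, but a high one cannot clear it, because a mapping that is biased or on the wrong scale can correlate just as well as a sound one.

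At stake is the conclusion on generalisability, which others might rely on where HUI-3 has not been measured. The reading of this trial's OM8-30-based QALYs is also affected, since QALYs depend on the utility scale itself.

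**Working it through.** **Inputs.** The aim, method, comparator and use of the mapped values come from the two sections quoted. The article gives no target correlation, error limit or expected utility, so there is no figure to reproduce. Assumed for illustration, and not from the documents: observed HUI-3 (U) with mean 0.80 and SD s_U = 0.20, mapped value (M) with correlation r = 0.70 to U, and normal distributions.

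**Step 1: invariance.** For any a and any b > 0,

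corr(a + bM, U) = b·cov(M, U) / (b·s_M·s_U) = corr(M, U).

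A rank correlation is unchanged too. In the extreme case M = 0.5 + 0.5U, r = 1.00, yet a true gain from 0.60 to 0.80 is mapped as 0.80 to 0.90, half its size. This step needs no assumed figure.

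**Step 2: what agreement measures would show.** With mean error d (mapped minus observed):

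- concordance coefficient (CCC) = 2·r·s_M·s_U / (s_M² + s_U² + d²)
- calibration slope of U on M = r·s_U / s_M
- RMSE = √(s_M² + s_U² − 2·r·s_M·s_U + d²)

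| Mapping | s_M | d | r | CCC | Slope | RMSE |
|---|---|---|---|---|---|---|
| Same spread as HUI-3, no shift | 0.20 | 0 | 0.70 | 0.056/0.080 = 0.70 | 0.70 | √0.024 = 0.155 |
| Shifted by +0.10 | 0.20 | 0.10 | 0.70 | 0.056/0.090 = 0.62 | 0.70 | √0.034 = 0.184 |
| Spread halved | 0.10 | 0 | 0.70 | 0.028/0.050 = 0.56 | 1.40 | √0.022 = 0.148 |
| Halved and shifted | 0.10 | 0.10 | 0.70 | 0.028/0.060 = 0.47 | 1.40 | √0.032 = 0.179 |

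A simulation with 302 children (the protocol's required number before allowing for loss) and 2,000 replicates gave the same r, mean error, CCC and slope to within rounding. Mean absolute errors were 0.123, 0.148, 0.118 and 0.144.

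The table needs two cautions. The first row is a reference, not an ideal: at r = 0.70 a calibrated mapping (slope 1) has s_M = 0.70 × 0.20 = 0.14. And halving the spread slightly lowers RMSE and absolute error, so error size alone would miss a scale fault. The calibration slope is needed as well.

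**Step 3: what reaches the QALYs.** A shift c that is equal in both arms at every visit cancels: (M₁ + c) − (M₀ + c) = M₁ − M₀. A scale fault does not. If the mapping multiplies the true between-arm utility difference by k, incremental QALYs are multiplied by k and the cost per QALY by 1/k:

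- k = 0.75: 1.33 times
- k = 0.50: 2 times
- k = 0.25: 4 times

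These values of k are illustrative. Getting from an individual-level slope to k needs a further assumption. If the line of U on M is the same in both arms at every visit, k = 1/slope, so a slope of 1.40 gives k = 0.71 and a slope of 0.70 gives k = 1.43. If instead the line of M on U is the stable one, k = r·s_M/s_U, which is 0.35 and 0.70 for the same two mappings. The answers differ, so mapped and observed between-arm differences should be compared directly. The trial's data allow this.

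**The case against.** **The method is left to the SAP.** A condensed article may leave detail to the analysis plan, and the choice of coefficient or the handling of repeated measures would be such detail. But the method for this check is stated, not left open. A SAP that follows the sentence literally inherits the fault.

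**A reader might infer that the trial's QALYs would come out wrong.** The documents do not support that. Nothing makes use of the mapped utilities depend on the correlation: the economic section computes QALYs from them with no threshold or gate. HUI-3 is collected directly, the questionnaires are repeated at each follow-up visit, and QALYs are also computed from HUI-3. A badly scaled mapping could be noticed as a gap between the two sets of results. This objection stands and confines the consequence. It does not rescue the check, because the article does not present that comparison as the test of the mapping.

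**A reader might also infer that a constant bias distorts cost per QALY, or that mapped scores are known to be compressed and hence biased.** The first fails when the shift is equal across arms and time, as Step 3 shows. The second has no source in the documents. Less spread than the observed scores is also not an error in itself: a calibrated prediction must have it. The fault to look for is a calibration slope away from 1, and nothing shows whether this mapping has one.

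**Conclusion.** The point holds as a mismatch between a stated aim and the method chosen for it. Correlation cannot establish that the mapping generalises, and this follows from algebra alone. The table's figures rest on the assumed SD and correlation. The cost-per-QALY multiples rest on assumed values of k, and no estimate of the actual error in this mapping can be drawn from the documents.

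The weight is moderate to low. The check is ancillary, and the primary outcome, the clinical comparison and the directly measured HUI-3 QALYs do not depend on it. What could be wrong is the published conclusion about the mapping and the confidence placed in the OM8-30-based QALYs. The change is worth making because it lets the trial answer the question it poses.

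**What to change.** Replace the sentence on correlation with a statement that the mapping will be judged by agreement between mapped and observed HUI-3, allowing for repeated measures per child. It should name:

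- mean error with 95% CI, and mean absolute or root mean squared error;
- calibration intercept and slope from regressing observed HUI-3 on the mapped value;
- error or limits of agreement across the utility range;
- mapped versus observed change from baseline, and mapped versus observed between-arm difference.

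Report correlation only as a supplement. Both instruments are already collected at baseline and each follow-up, so no new data are needed. The cost is a sentence or two of text and a little more analysis.

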#### Economic analysis/cost effectiveness analysis

The cost-effectiveness analysis will be conducted from the perspective of the UK NHS and Personal Social Services and also will consider a broader partial societal perspective, encompassing impacts on patients and their families. The cost-effectiveness component will have two time durations: a within-trial assessment and a longer term time horizon based on decision-analytic modelling and populated from parameter estimates derived from the trial and from information from literature sources relating to long-term effects of hearing difficulties in children. These time periods offer a longer duration than previous studies and will be used, alongside other sources, to arrive at more meaningful estimates of cost-effectiveness.

The costs of the course of oral steroids will be calculated and combined with differences in costs between intervention and control groups to determine overall costs associated with the intervention. The resource utilisation of both groups (consultations, medications, operations, equipment, etcetera) and treatments associated with adverse events, will be assessed through the completion of self-completed questionnaires at baseline, at 5 weeks, 6 months and 12 months and translated into costs using appropriate published unit costs [29].

The difference in overall costs between groups will be compared with differences in outcomes, as specified above, and including quality-adjusted life years (QALYs). QALYs will be computed from PedsQL and HUI 3 and from utilities derived from mapping responses to the OM8-30 questionnaire [30].

A series of one-way sensitivity analyses will be conducted to assess the impact of parameter variation on baseline estimates of the cost-effectiveness ratios and a probabilistic sensitivity analysis undertaken to determine the extent to which the intervention can be regarded as representing value for money.

